### Sample size calculations

For the purpose of sample size estimation, the primary outcome of this study was difference in BMI Z-score at 12 weeks. Our own pilot data, and data from the largest RCT in obese adolescents yet published (209 children aged 8-16 with BMI > 95^th^ percentile; Savoye 2007) suggest the standard deviation in BMI Z-score in a non-passive weight loss intervention will be approximately 0.27. Assuming a 2-sided 0.05 significance level, a sample size of 52 participants per group would provide 80 % power to detect a clinically important treatment difference of 0.15 BMI Z-score. To account for a 25 % drop-out, we plan to enrol 70 participants in each group.

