### Recruitment and randomisation

The study will be advertised within the weight management centres in Victoria, Western Australia, New South Wales and the Australian Capital Territory as well as on the company website. Potentially eligible clients will be assessed in the weight management centres by consultants, guided by dietitians and/or a general practitioner for study eligibility. If participants who meet eligibility criteria are interested in participating in the study, they will be shown an information DVD. All participants will provide written consent that will be obtained by consultants in the weight loss centres from both the adolescent and their parent or guardian. Consenting adolescents will then be recruited into the study via telephone by a researcher.

Allocation to treatment group (intervention or wait-listed control) will occur using computer-generated random numbers. Group allocation will occur off-site by a statistician with no day-to-day study involvement in the trial. Individuals will be allocated 1:1 to the intervention group or wait-listed. Randomisation of the study participants will be stratified by the weight-management centre from which they are enrolled. Within each centre, randomisation will occur in blocks of either 6 or 8. Block size will be randomly selected and unknown to anyone except the study statistician ([name]). Treatment allocation will be stored in an online database, accessible only by the study statistician, and will remain unknown until revealed to the study co-ordinator on the day each participant is allocated to a treatment group. Due to the nature of the intervention masking participants to group allocation is not possible.

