### Intervention: the JenMe program

A 12 week evidence-based lifestyle intervention program was developed by the team of Accredited Practising Dietitians at Jenny Craig Australia and was reviewed for content by paediatric psychologists specialising in behaviour change. The program will be delivered face to face to clients in the Jenny Craig Centres by consultants on a weekly basis for the duration of the program. Consultants in the centres have been trained by Jenny Craig and are not otherwise required to be trained health professionals. Specialised program materials will be used with participants and their parents or guardians. The participants will present to the centre to meet with a consultant weekly for 13 consecutive weeks (Weeks 0 to 12). Each week, a new element of the program (Table 1) will be delivered at each consultation to the adolescent, who will be encouraged to modify small behaviours each week. The order of topic deliverance will be directed by the adolescent and tailored to their needs. The parent or guardian will be involved in part of the consultation to ensure participation in the goal setting process. The program also encompasses a dietary plan that has been modelled on the dietary guidelines as outlined by the National Health and Medical Research Council’s (NHMRC, 2013) Australian Dietary Guidelines [22].

**Table 1 Tab1:** Topics covered over 12 weeks within the JenMe program

Eat Well		Move more	Live life
▪ Decoding drinks		▪ How to move more by tracking how you move less	▪ Body image
▪ Eating out for success		▪ Overcoming your activity barriers	▪ Learning from lapses
▪ Jenny at school & friends’		▪ Setting SMART goals	▪ Rewards & buddies
▪ Meals with the family and fast & healthy after school snacks		▪ Time for a physical activity challenge!	▪ Saying No
▪ Non-hungry eating & learning to eat with awareness			

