### Statistical analysis plan

Summary descriptive statistics for demographic and clinical data at baseline will be reported by allocated study treatment. Continuous data will be summarised descriptively using either mean and standard deviation, or median and inter-quartile range, depending on the distribution of the variable of interest. Categorical data will be presented as frequencies and percentages. Comparisons between the treatment groups will be conducted to assess the degree to which comparability of randomisation was achieved.

The primary study outcomes are between-group differences in age and gender adjusted BMI Z-score and waist-to-height ratio at 12 weeks. The mean difference between treatment groups will be calculated using linear regression with treatment group entered as the main effect and covariable adjustment for baseline outcome. The corresponding 95 % Wald confidence interval and p-value will be reported. For secondary outcomes, the effect estimate relating to a variable with a binary outcome will be presented as an odds ratio, which will be calculated using a logistic regression model. The effect estimate relating to a variable with a continuous outcome will be presented as a mean difference, which will be calculated using a linear regression model. The effect estimate relating to a variable with a count outcome will be presented as an incident rate ratio, which will be calculated using a Poisson regression model. For all models considering outcomes measured at 12 weeks, the baseline outcome will be included as a covariable. For all models the corresponding 95 % Wald confidence interval and p-value will be reported.

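### The 12-week models ignore both the consultants who deliver the program in one arm and the centres used to stratify, so the confidence interval may be miscalibrated in either direction

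*Protocol article*

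**What the plan says.** Under Intervention: the JenMe program, consultants in the centres deliver 13 weekly face-to-face sessions (weeks 0 to 12). They are trained by the company and "are not otherwise required to be trained health professionals". Under Wait-listed control, the other arm receives a healthy-eating booklet and advice to keep current habits, with the program offered only after 12 weeks. Under Anthropometry, consulting staff take the baseline measurements of all participants, so consultants do have contact with controls.

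Under Recruitment and randomisation: "Individuals will be allocated 1:1 to the intervention group or wait-listed". Allocation is stratified by centre, in blocks of 6 or 8.

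Under Statistical analysis plan, the 12-week primary analysis is fixed: "The mean difference between treatment groups will be calculated using linear regression with treatment group entered as the main effect", with adjustment for the baseline outcome and a Wald interval. The secondary linear, logistic and Poisson models name no centre or consultant term either. The sensitivity analyses add only participant characteristics. The one random effect in the plan is for participant, in the six-month models.

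Under Sample size calculations, with a two-sided alpha of 0.05, an SD of 0.27 and a target difference of 0.15, the article states that "a sample size of 52 participants per group would provide 80 % power". No ICC, cluster size or design effect enters.

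**The concern.** Participants treated by the same consultant may have correlated outcomes. That correlation arises through treatment, so it exists in the intervention arm only: the design is partially nested. Ordinary regression assumes independent residuals in both arms. A centre term shared by both arms does not remove the consultant effect, because the treatment itself carries it.

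The model also drops the centre by which randomisation is stratified. Blocking makes the arms similar in centre mix. If centres differ, that shared variation largely cancels from the treatment comparison but stays in the residual variance, and so makes the reported standard error too large.

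The article thus fixes a model that ignores two sources of structure acting in opposite directions. At stake is whether the intervals and p-values for both primary outcomes, and for the 12-week secondary outcomes, mean what they say.

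**Working it through.** **1. Inputs from the Sample size section.** Two-sided alpha 0.05, power 80%, difference 0.15, SD 0.27, 52 per group analysed, 25% drop-out, 70 per group enrolled.

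**2. Reproducing the plan's figure.** n per group = 2 × (1.960 + 0.842)² × (0.27/0.15)² = 50.9, so 51 by the normal approximation. The noncentral t gives 79.3% power at 51 and 80.1% at 52, so 52 is the t-based answer. Enrolment is 52/0.75 = 69.3, so 70. The stated figures are reproduced with a design effect of 1, that is, with independent participants and almost no slack.

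**3. Consultant variation alone.** Assumptions, since the article gives neither: m of 2 to 5 intervention participants per consultant and an ICC of 0.02 to 0.10. As a guide to m, a full block of 6 or 8 puts 3 or 4 intervention participants in one centre, though not necessarily with one consultant.

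- Intervention-arm design effect: DE = 1 + (m−1) × ICC.
- True over reported standard error: r = √((1 + DE)/2).
- Type I error of the planned test: 2 × (1 − Φ(1.96/r)).
- Power of a valid 5% test, taking the stated 80% as the base: Φ(2.802/r − 1.960).
- Rejection rate of the planned test at 0.15: Φ(0.842/r).

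| m | ICC | DE | r | Type I error, planned test | Power, valid test | Rejection at 0.15, planned test |
|---|---|---|---|---|---|---|
| 2 | 0.02 | 1.02 | 1.005 | 5.1% | 79.6% | 79.9% |
| 3.5 | 0.05 | 1.125 | 1.031 | 5.7% | 77.6% | 79.3% |
| 5 | 0.10 | 1.40 | 1.095 | 7.4% | 72.5% | 77.9% |

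An r of 1.095 means that the true standard error is 9.5% larger than the reported one; equivalently, the reported one is 8.7% too small (1 − 1/1.095).

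A simulation of the unadjusted two-group comparison (20,000 runs per setting, 52 per arm) agrees. At m = 5 it gives type I error of 6.1% (ICC 0.05) and 7.0% (ICC 0.10), with rejection at 0.15 of 78.9% and 77.8%. At m = 1 type I error is 4.8% to 5.2%, so the problem vanishes.

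**4. Adding centre.** Let σu² be the consultant variance, σc² a centre variance shared by both arms, σe² the rest, and n the number per arm. Suppose that blocking balances centres across arms.

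- True variance of the difference: (2σe² + mσu²)/n.
- Variance that the planned model reports: (2σe² + σu² + 2σc²)/n.
- True minus reported: [(m−1)σu² − 2σc²]/n.

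The planned interval is therefore too narrow only when (m−1)σu² exceeds 2σc². In the middle row of the table the two cancel when the centre share of variance is (2.5 × 0.05)/2 = 0.0625, about 0.06. Above that the planned interval is too wide.

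**The case against.** Everything quantitative beyond the base sample size is assumed. Recruitment covers centres in three states and one territory, for 70 intervention participants. Many consultants may treat only one, and then nothing is lost. Company training, specialised materials and a set list of topics limit variation between consultants, and the article does not guarantee one consultant for all 13 sessions. Baseline adjustment could also recover precision. If 0.27 is the SD of the 12-week value, which the article does not say, a baseline correlation of about 0.24 restores the precision lost in the middle row (1 − 0.24² ≈ 1/1.031²). The article calls the evaluation a first step, so inference limited to the participating consultants could be defended. All of this bears on size, and it stands.

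The objection that a journal article may leave provider clustering to a fuller plan carries less weight. This article states its model, and the model assumes independence.

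Three stronger readings are tempting but not supported:

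- *The error bars are too narrow.* Omitting centre pushes the other way, and the documents do not show which effect dominates.
- *The planned analysis loses both power and error control to the extent tabulated.* The fall to 72.5% belongs to a corrected test. The planned test keeps rejecting close to 80% of the time, at the price of a type I error above 5%.
- *Controls have no contact with consultants.* Consulting staff measure them as well. Only the treatment is one-armed, and measurement variation linked to staff can arise in both arms.

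**Conclusion.** The point holds as a conditional weakness of a stated model, not as a figure shown to be wrong. The sample size arithmetic is correct on its own terms. The 12-week models ignore consultant clustering in the intervention arm and the centre stratum in both arms, and nothing in the article establishes that either is negligible or that they cancel.

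The table gives the size for consultant variation alone, under its assumed ICC and m: negligible at the low end, and a type I error of about 7% at the high end. Centre variation can offset or reverse this. A reader might infer that the trial is underpowered or that its conclusions will be overconfident; the documents do not support either as a flat statement. The change is worth making because it costs little and accounts for both sources of variation, whichever dominates.

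**What to change.** 1. Record the treating consultant for each intervention participant.
2. Include the centre stratum in all 12-week models.
3. Account for consultant in the intervention arm only. For continuous outcomes, use a random consultant effect with controls as singletons, arm-specific residual variance and small-sample degrees of freedom (Satterthwaite or Kenward-Roger). For logistic and Poisson outcomes, use a corresponding random effect or cluster-robust errors.
4. Specify a fallback: if most consultants treat one participant and the variance cannot be estimated, report the centre-adjusted model, with the consultant model as a sensitivity analysis.
5. State in the sample size section that the 80% power assumes no consultant clustering, and give the range over assumed ICCs. Leave enrolment at 70 per group.

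The cost is one extra recorded field, some analysis-plan wording and slightly wider intervals where consultants differ. Enrolment, visits and treatment do not change.

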The initial approach to all analyses will be based on the ‘intention to-treat’ (ITT) principle, where all evaluable data is analysed in the treatment group according to which the participant was allocated. Additionally, because of the potential for differential between-group attrition due to the nature of recruitment, all analyses will be investigated to see whether results are sensitive to possible between-group imbalances in key demographic, social, or clinical characteristics. Characteristics of participants for whom follow-up data is available will be compared between groups, and variables significantly different at P < 0.05 will be identified. Multivariable regression models will be run with treatment group as the main effect and covariables including the value of the outcome at baseline and characteristics identified as differing between treatment groups at follow-up. All sensitivity analyses will be clearly labelled., Statistical significance will be defined as alpha = 0.05. All tests conducted will be two-tailed.

Outcomes measured at six months will be analysed using mixed-effects regression models with a random intercept for each participant. For continuous outcomes Gaussian family and identity link function, for binary outcomes a binomial family and logit link function, and for count outcomes a Poisson family and log link function will be used. All models will include time period (baseline/12 weeks/36 weeks) as a main effect, and other covariables will be included as appropriate.

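### Randomisation is stratified by centre, but the primary 12-week regression leaves centre out; if centre is prognostic, the test is mildly conservative and some precision is lost

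*Protocol article*

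**What the plan says.** Under Recruitment and randomisation, the protocol article states: "Randomisation of the study participants will be stratified by the weight-management centre from which they are enrolled". It adds: "Within each centre, randomisation will occur in blocks of either 6 or 8". The ratio is equal: "Individuals will be allocated 1:1 to the intervention group or wait-listed". Centres in four Australian states and territories advertise the study; their number is not given.

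Under Statistical analysis plan, the mean difference for both primary outcomes comes from "linear regression with treatment group entered as the main effect and covariable adjustment for baseline outcome", with a Wald 95% interval and p-value. The same covariable rule is then generalised: "For all models considering outcomes measured at 12 weeks, the baseline outcome will be included as a covariable". No other covariable is named for the main 12-week models.

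Two further model descriptions in that section do not bring centre in either:

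- The sensitivity models use "covariables including the value of the outcome at baseline and characteristics identified as differing between treatment groups at follow-up". These characteristics are selected by a between-group test at P < 0.05.
- The six-month models are "mixed-effects regression models with a random intercept for each participant". They allow other covariables as appropriate, but they concern the later follow-up, which covers the intervention group only.

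**The concern.** Centre is built into the allocation and then dropped from the analysis. Blocking within centre makes the arms similar in centre mix, so most between-centre variation cancels from the treatment difference. A regression without centre does not know this: it leaves the between-centre variance in the residual and computes its standard error as if allocation had been unrestricted. The interval is then wider than the design warrants.

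This matters only if centre is related to the 12-week outcome, in both arms, after baseline adjustment. That is plausible. The Anthropometry section has centre staff take the measurements (stated outright for baseline), so operator differences could enter both primary outcomes. The centres are also spread over regions, and the Background section reports that overweight and obesity vary with area-level socioeconomic status. At stake is part of the precision that stratification was meant to give, in a trial planned at about 80% power with little to spare.

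**Working it through.** **Inputs from the document** (Sample size calculations, Recruitment and randomisation): difference 0.15; SD 0.27; "Assuming a 2-sided 0.05 significance level"; 52 evaluable per group; 25% drop-out; 70 enrolled per group; blocks of 6 or 8 within centre.

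**Assumptions, because the document gives no figure:** centre ICC of 0.05, 0.10 or 0.20; 5 to 40 centres; 0.27 taken as the residual SD after baseline adjustment.

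**1. The plan's own figure.** The normal approximation gives 51 per group and the t distribution gives 52 (power 80.1%). Drop-out: 52 / (1 − 0.25) = 69.3, so 70. The stated sample size reproduces and is not in question.

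**2. Upper bound: exact 1:1 balance within every centre.**

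- Model SE without centre = 0.27 × √(2/52) = 0.0530.
- True SE = 0.0530 × √(1 − ICC).
- Excess width = 1/√(1 − ICC) − 1.
- Type I error = 2 × [1 − Φ(1.96/√(1 − ICC))].
- Power without centre = Φ((0.15 − 1.96 × 0.0530)/true SE).
- Power with centre = Φ(0.15/true SE − 1.96).

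| ICC | True SE | Excess width | Type I error | Power without centre | Power with centre |
|---|---|---|---|---|---|
| 0 | 0.0530 | 0 | 5.0% | 80.9% | 80.9% |
| 0.05 | 0.0516 | 2.6% | 4.4% | 81.5% | 82.8% |
| 0.10 | 0.0502 | 5.4% | 3.9% | 82.1% | 84.8% |
| 0.20 | 0.0474 | 11.8% | 2.8% | 83.5% | 88.6% |

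**3. Realistic balance.** With 140 participants in blocks of 6 or 8 there are only about 20 blocks, so many are left unfilled, and drop-out unbalances centres further. Simulation with stratified blocks, unequal centre sizes and 25% random drop-out gave the following at ICC 0.20. Excess width is model SE divided by empirical SE, minus 1.

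| Centres | Model SE | Empirical SE | Excess width | Type I error |
|---|---|---|---|---|
| 5 | 0.0514 | 0.0472 | 8.9% | 2.9% |
| 10 | 0.0521 | 0.0491 | 6.1% | 3.9% |
| 20 | 0.0524 | 0.0493 | 6.3% | 3.9% |
| 40 | 0.0526 | 0.0504 | 4.4% | 4.1% |

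Monte Carlo error on the excess is about 1 percentage point. Taken with repeat simulations of the same setting, the excess is about 0–1.5%, 3% and 5–7% at ICC 0.05, 0.10 and 0.20. Type I error is about 5%, 4–5% and 3.5–4%.

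**4. Form of the centre term.** Simulated power at ICC 0.10, with the random-intercept column treating the ICC as known:

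| Centres | No centre term | Fixed effects | Random intercept |
|---|---|---|---|
| 5 | 81.5% | 83.6% | 84.5% |
| 10 | 82.1% | 83.9% | 84.4% |
| 20 | 80.4% | 79.8% | 84.3% |
| 40 | 81.5% | 71.3% | 82.4% |

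At ICC 0.20, power without a centre term and with a random intercept was 82.9% and 87.3% (5 centres), 83.0% and 86.6% (10), 82.2% and 86.9% (20), and 82.4% and 84.9% (40). Allowing for simulation error, the loss from omitting centre is roughly 1, 2–3 and 4–5 points at the three ICCs, and less with many small centres.

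**The case against.** The strongest reply is that this is a small, conditional loss in the safe direction. The residual centre effect after baseline adjustment may be near zero. Even on the upper-bound figures, the planned model keeps 81.5% to 83.5% power, above the stated 80%. All of that stands, and it limits the point to a modest improvement.

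A second reply is that a journal article condenses the plan, so centre may appear in a fuller document. That could be so. But the article does not leave the covariables open: it names them, and for the main 12-week models the list is the baseline outcome alone.

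Some stronger readings are tempting but not supported:

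- A reader might infer that intervals and p-values for every 12-week outcome are miscalibrated. The document gives no ICC, so this cannot be said unconditionally. The √(1 − ICC) result is for linear models and does not carry over directly to the logistic and Poisson models. The blood and DXA outcomes come from opt-in subsets that randomisation did not balance by centre.
- A reader might take the 11.8% excess and 2.8% type I error as expected values. They require exact within-centre balance and are bounds.
- A reader might count unfilled blocks as a second error. The resulting chance imbalance is already reflected in the unadjusted standard error; it mainly shrinks the gap.
- A reader might cite local delivery of the program as the reason the interval is too wide. Delivery reaches only the intervention arm, since controls receive a booklet. Variation in delivery is therefore centre-by-treatment variation and could work the other way. With an intervention-arm-only ICC of 0.10 and 10 centres, simulation gave a model SE of 0.0526 against an empirical 0.0589, if inference is to centres in general.

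**Conclusion.** The point holds as a minor to moderate mismatch between design and analysis. The primary linear models omit the one factor on which randomisation was stratified, and the document gives no reason. If centre is prognostic in both arms given baseline, the consequence is a mildly conservative test and forgone precision of the size shown above. A shared centre effect of this kind neither biases the estimate nor inflates type I error, and the trial's validity is not threatened. The size rests on the assumed ICC and number of centres, and on reading 0.27 as the SD after baseline adjustment. The random-intercept gains are slightly optimistic because the ICC was treated as known.

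**What to change.** Add centre as a random intercept to the 12-week linear models for BMI Z-score and waist-to-height ratio, and to those for the continuous secondary outcomes measured in all participants. Keep treatment group and baseline outcome as planned. State the form in advance, and do not use fixed centre effects, which cost power if there are many small centres.

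The cost is small. Centre is already recorded for randomisation, and the model gains one variance component, which may be estimated as zero. In that case the result is essentially that of the planned model.

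A centre-by-treatment random slope is optional as a sensitivity analysis. It would address variation in delivery within the intervention arm and could widen the interval, but it may not be estimable with small centres. If the fuller analysis plan already includes centre, the two descriptions need only be aligned.

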#### Physical activity

In order to monitor physical activity levels, the adolescents in both groups will be required to complete the Adolescent Physical Activity Recall Questionnaire (APARQ), which has been validated in an Australian population [25]; and complete a 4-day activity diary (Children’s Nutrition Centre, University of Queensland, Australia). A pedometer will be worn over the 4- day period and number of steps will be recorded in the activity diary. This will be performed both in the week prior to commencement of the intervention or wait-listed period and repeated at 12 weeks.

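### Count outcomes are fixed to Poisson regression with no provision for overdispersion; if pedometer steps are analysed under that rule, their standard errors would be too small by a factor of tens

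*Protocol article*

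**What the plan says.** The section Statistical analysis plan assigns a model to each type of secondary outcome: logistic for binary, linear for continuous, Poisson for counts. A count effect is an "incident rate ratio, which will be calculated using a Poisson regression model". For continuous variables, "The effect estimate relating to a variable with a continuous outcome will be presented as a mean difference". Two rules then apply throughout: "For all models considering outcomes measured at 12 weeks, the baseline outcome will be included as a covariable", and "For all models the corresponding 95 % Wald confidence interval and p-value will be reported".

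For the follow-up at 36 weeks the same section specifies mixed-effects models with a random intercept per participant, and "for count outcomes a Poisson family and log link function will be used". Neither part mentions overdispersion, a scale parameter, negative binomial regression or a robust variance. The sensitivity analysis it describes adds covariates that differ between groups; this leaves the variance assumption as it is.

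The section Physical activity says: "A pedometer will be worn over the 4- day period and number of steps will be recorded in the activity diary". It does not say whether steps are analysed as a count or as a continuous variable, or as a daily mean or a four-day total. Change in physical activity is named as a secondary outcome under Study design and participants.

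**The concern.** A Poisson model sets the variance equal to the mean. Step counts run to thousands per day, and people differ from one another by thousands, so the between-person variance is hundreds of times the mean or more. A standard error computed under the Poisson assumption then reflects only a small fraction of the real variation.

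The number of steps is literally a count, so an analyst applying the plan's rule by variable type could put it in the Poisson model, and nothing in the article prevents that. A trivial chance difference in steps could then be reported as a highly significant programme effect with a very narrow interval. The linear model in the same section would give ordinary inference for the same data. The two permitted readings therefore differ radically, and the choice between them is not fixed in advance.

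**Working it through.** **The plan's own figures.** The article gives no mean, SD or dispersion for steps. Its sample size concerns BMI Z-score and reproduces: 2 × (1.96 + 0.84)² × (0.27/0.15)² gives 51 per group by the normal approximation and 52 by the t-test, and 52/0.75 rounds up to 70. It does not bear on this point, except that 52 evaluable per group is used below.

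**Assumed inputs.** Daily mean 9,000 steps, between-person SD 2,000 to 4,000; wider range: mean 5,000 to 12,000 with the same SDs. Correlation between baseline and 12 weeks: r = 0.5 or 0.7. None of these is in the article.

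**Formulas.**
- Factor by which the Poisson standard error is too small: k = √(SD²/mean) = SD/√mean.
- After baseline adjustment: k × √(1 − r²).
- True type I error of a nominal 5% test: 2 × [1 − Φ(1.96/k)].

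**12 weeks, mean 9,000:**

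| SD | variance/mean | k unadjusted | type I error, unadjusted | k at r = 0.5 | k at r = 0.7 |
|---|---|---|---|---|---|
| 2,000 | 444 | 21.1 | 0.926 | 18.3 | 15.1 |
| 3,000 | 1,000 | 31.6 | 0.951 | 27.4 | 22.6 |
| 4,000 | 1,778 | 42.2 | 0.963 | 36.5 | 30.1 |

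In steps, for SD 3,000, 52 per group and no adjustment: the true standard error of the log ratio is √(2/52) × 3,000/9,000 = 0.065, so a 95% interval is about ±13% (about 1,150 steps per day). The Poisson standard error is √(2/(52 × 9,000)) = 0.0021, so the interval is about ±0.4% (about 36 steps per day).

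**Wider range.** Unadjusted, k runs from 18 (12,000/2,000) to 57 (5,000/4,000). Adjusted, it is 16 to 49 at r = 0.5 and 13 to 40 at r = 0.7. At the lowest value, k = 13, type I error is 2 × [1 − Φ(0.151)] = 0.88.

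**Four-day total.** If the SD is that of the four-day average, mean and SD are both multiplied by 4, so k becomes 4·SD/√(4·mean), which is twice the daily value: about 37 to 113 unadjusted.

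**Simulation check.** No treatment effect, 52 per group, gamma-distributed steps, baseline as covariate on the log scale, 1,000 runs each:

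| mean/SD, r | mean ratio of robust to Poisson SE | type I, plain Poisson | type I, robust (HC1) |
|---|---|---|---|
| 8,000/3,000, 0.5 | 28.6 | 0.946 | 0.061 |
| 8,000/2,000, 0.5 | 19.0 | 0.920 | 0.051 |
| 10,000/4,000, 0.5 | 34.1 | 0.947 | 0.057 |
| 6,000/2,500, 0.7 | 22.7 | 0.946 | 0.050 |

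**36 weeks.** The random intercept absorbs stable differences between people. Variation within a person is still taken as Poisson. Its SD relative to the Poisson SD is SD × √(1 − r)/√mean: 23.7 for 8,000/3,000 at r = 0.5, 18.4 at r = 0.7, and 11.0 for 10,000/2,000 at r = 0.7.

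**Low counts.** With an assumed mean of 5 and SD of 4, k = 4/√5 = 1.8. In a simulation with variance/mean = 3, plain Poisson gave 25% false positives. The article names no such outcome, so this shows only how the rule behaves.

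**The case against.** The strongest objection is that the article never assigns steps to the Poisson model. The plan is a generic rule by variable type and places no secondary variable under any type. A daily average in the thousands fits naturally under the linear model in the same section, in which case steps are analysed soundly. A reader might infer that, as written, the trial will report step differences with standard errors 20 to 40 times too small. The document does not support that: the classification is open, and the size comes from an assumed mean and SD. This part of the objection stands, and the point is conditional for that reason.

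Second, a condensed article may leave dispersion checks and the variance estimator to a full analysis plan, and a Wald interval can be built on a robust or scaled variance. It is true that nothing rules these out. But the article does more than stay silent: it names the model, family, link and interval type for counts at both time points, and an analyst could follow that text literally without departing from it.

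Third, steps are the only evident count of any size. The claim that other outcomes would be affected has no named variable behind it and is not made here.

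Fourth, the 36-week follow-up covers the intervention group only, so the between-group type I error figures do not carry over to it. That is right; what remains there is the unmodelled within-person variation, which affects comparisons over time.

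**Conclusion.** The point holds in conditional form. The plan fixes Poisson regression for all count outcomes with no provision for overdispersion, and leaves open whether the one evident large count falls under that rule. If steps are analysed as a daily count, the 12-week standard error is too small by about 20 to 40 unadjusted under the assumed mean of 9,000 and SD of 2,000 to 4,000. With the baseline adjustment that the plan requires, it is roughly 13 to 40 (r = 0.7, wider inputs). A four-day total doubles the factor.

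Type I error is above 90% in the unadjusted cases and in all four baseline-adjusted simulations, and about 88% at the most favourable corner of the range. The exact factor depends on the assumptions; that the p-value would be unusable does not, within any range tried. At 36 weeks the random intercept removes only the between-person part.

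Both primary outcomes, BMI Z-score and waist-to-height ratio, use linear regression and are unaffected, as is the sample size. This is a matter for a named secondary outcome and should be settled before analysis.

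**What to change.** State that pedometer steps are analysed as a continuous outcome, with the baseline-adjusted linear model at 12 weeks and the Gaussian mixed model at 36 weeks, both already in the plan, and say whether the variable is the daily mean or the four-day total. For any true low-count outcome, specify Poisson regression with a robust (sandwich) variance or negative binomial regression, and make the same allowance for overdispersion in the 36-week count models.

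The cost is a sentence or two of analysis plan wording. The methods are standard software options, and no change to data collection or sample size is needed.
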